**Side view** **(right and left)**				

***Criteria***	***Description***	***Observation***	***Measurement***	***Score***

Knee angle *- First foot contact* *- Maximal knee flexion*		Knee angle at first foot contact Knee angle at maximal knee flexion	Ankle between trochanter major - caput fibulae (tractus iliotibialis) - mallolus externus	Degrees:

Hip angle *- First foot contact* *- Maximal knee flexion*		Knee angle at first foot contact Knee angle at maximal knee flexion	Angle between trunk - trochanter major - caput fibulae (tractus iliotibialis)	Degrees:

Ankle angle *- First foot contact* - *Maximal knee flexion*		Knee angle at first foot contact Knee angle at maximal knee flexion	Angle between caput fibulae (tractus iliotibialis) - malleolus externus - parallel with sole of foot	Degrees:

*'shoulders above knees'*		Position at maximal knee flexion	Perpendicular through centre of shoulder (humerus head)	Perpendicular through caput fibula: 0 Perpendicular not through caput fibula: 1

*'knees not further than toes'*		Position at maximal knee flexion	Perpendicular through centre of knees	Perpendicular not further than toes: 0 Perpendicular further than toes: 1

*'forefoot landing and rolling to heel'*	Forefoot landing and rolling to heel	Observe complete jump	Pattern present or not	Pattern present or doubt: 0 Pattern not present: 1

*Arm swing*	Obvious arm swing that contributes to the jump height	Observe complete jump	Arm swing present or not	Arm swing present: 0 Arm swing not present: 1

#### Exposure time

Exposure is recorded by the coach on an exposure form. Coaches note the total duration of each training session and match, and classify the level of participation of each player (that is, in terms of full, three quarters, one half, one quarter, or no participation). If the player does not participate fully, the coach note the reason--that is, being injured, ill, or absent for other reasons. Completed exposure forms are returned on a weekly basis. Every week trainers are contacted by phone and urged to fill out the exposure sheets, and, if necessary, the injury forms. In this, we followed the example of Verhagen et al.[2] who applied the same method of exposure registration.

#### Injury definition

To determine the effectiveness of the program for the prevention of injuries, all injuries that occur during the entire season are registered in both the IG and CG. Injuries are divided into two main categories: acute or overuse injuries. An acute injury is defined as a sports accident, with a sudden, direct cause/onset, which requires at least minimal (medical) care (e.g. ice or taping) and which causes the injured subject to miss out on at least 1 training session. Exclusion criteria involve muscle cramps and mild bruises. A subject sustains an overuse injury if he or she experiences a physical discomfort, with an insidious onset, that caused pain and/or stiffness of the musculoskeletal system, and that is present before, during and/or after the sports activity. The overuse injury is only registered if present for at least three consecutive sessions. Illness and fatigue are not registered as overuse injuries [18].

#### Injury registration

Coaches receive injury forms at the start of the study. In case of injury, the coach completes in concordance with the injured player injury registration forms, which have to be completed within one week after injury onset. On this form the player is asked to provide information on the injury location, injury type, diagnosis of the injury, direct cause of the injury, preventive measures used at the time of the injury, first aid given, and subsequent medical treatment. If an injury is noted on the exposure form and no injury registration form is received within two weeks after the injury is logged, the coach is contacted and urged to let the player complete the injury registration form.

### Process evaluation & Compliance

Coaches are contacted on a weekly basis by means of a telephone call. The goal of this call is to inquire about the ongoing of the study and to follow-up on any missing exposure or injury registration forms. In addition, IG coaches are asked whether they followed the prescribed exercises for that particular week. If not, the exercises that are carried are noted in order to gain insight into the compliance to the program.

At T1 coaches are required to complete a questionnaire inquiring on their opinion of the intervention program, their compliance to the prescribed exercises, and to inquire about any difficulties in executing the program.

### Statistical analyses

The injury incidence density (IID) is calculated as the number of new injuries per 1,000 hours of participation, using exposure time of each individual participant until the first injury. The number of injuries divided by the total time at risk is the preferred measure of incidence because it can accommodate variations in the exposure time of individuals [34,35]. If an athlete suffers multiple injuries, only the first injury will be considered in the analysis.

Because the unit of allocation was teams, we perform a multilevel Cox proportional hazard regression analysis, using the computer based software SPSS 17.0 (SPSS Inc, Chicago, Illinois, USA), to estimate the hazard ratios (HRs) and 95% confidence intervals (CIs). Teams will be used as cluster levels [36].

The difference between the CG and IG regarding the JLS-system is calculated using Repeated Measures ANOVA (p < 0.05) for normally distributed data and the Mann-Whitney-*U *test (p < 0.05) for data which are not normally distributed.

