### Research questions

- What is the effectiveness of a coach supervised jump landing intervention program on the incidence of acute and overuse injuries to the lower extremity?

- What is the effect of a coach supervised jump landing intervention program on jump landing technique of individual athletes?

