### Sample size

A power calculation is carried out for the main outcome variable lower extremity injury incidence. A difference of 50% in the incidence of lower extremity injuries between the intervention and control group after a follow up of one season is considered to be clinically relevant.

The prevalence of lower extremity injuries in basketball in Flanders being about 78% in one season [6], 34 subjects per group are needed to detect the intended difference of 50% in the incidence of lower extremity injuries, with a power of 90% and an alpha of 5%. Assuming a dropout rate of about 20% a total of 82 athletes are needed to detect a potentially clinically relevant effect of the intervention. However, as teams serve as unit of randomization, a cluster effect should be taken into account. Therefore, an intra-cluster correlation coefficient of 20% was considered, resulting in a total of 240 athletes from 24 teams is necessary at baseline.

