### Measurements

During the study period there are two fixed measurements, at baseline (T0) and after 3 months (T1). At T0 a questionnaire is completed by the athletes, and at both occasions the athletes' jump landing technique is assessed. Additionally, exposure hours and lower extremity injuries are continuously registered during the entire 2010-2011 basketball season (6 months).

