#### Jump landing technique

An improvement in jump-landing technique is determined by registering jump-landing technique of athletes in the CG and IG. Athletes are asked to perform 3 separate maximal vertical jumps which are recorded on camera (SONY HDV 1080i). The researchers collect the jump-landing data at T0 and T1. These jumps are all analyzed through the computer program Darttrainer^®^. In addition, all jumps are evaluated through a predefined list of criteria, the JLS-System (Jump-landing Scorings system) (Table 2). This tool is developed as a field test to evaluate proper jump-landing technique.

**Table 2 T2:** Scorings system Jump-landing Technique (JLS-system)

Front view (observers view)				
***Criteria***	***Description***	***Observation***	***Measurement***	***Score***

Maintaining 'balance' *- Loss of balance*	Lifting one foot or toes of both feet due to falling.	Observe complete jump	Loss of balance present or not	Loss of balance not present or doubt: 0 Loss of balance present: 1
*- Centre of gravity displacement*		At first foot contact: Perpendicular through incisura jugularis	At maximal knee flexion determine the position of incisura jugularis (left/right) compared to perpendicular	Displacement not present or doubt: 0 Displacement left or right: 1

Landing with '*both feet at the same time'*	Not simultaneous: obviously 2 contact times of the feet visible	Observe complete jump	Simultaneous landing present or not	Simultaneous landing present or doubt: 0 Simultaneous landing not present: 1

*'Muscular control' *during landing	Presence of eccentric control during landing, capacity to lower the body in a controlled manner (no side movements of the knee, no sudden stops)	Observe complete jump	Muscular control present or not	Muscular control present or doubt: 0 Muscular control not present: 1

*'Genu varum' - 'Genu valgum' take-off*	Malalignement: valgus or varus position	At maximal knee flexion: perpendicular from SIAS to ankle (middle of malleoli) - Take-off	No varum or valgum: perpendicular goes through centre of patella	Perpendicular through patella or doubt: 0 Patella lateral from the perpendicular: (1 = varum) Patella medial from the perpendicular: (2 = valgum)

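### The two-time-point Repeated Measures ANOVA for jump-landing technique does not adjust T1 for T0 and leaves its group contrast unnamed: a minor loss of efficiency

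*Protocol article*

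**What the plan says.** The second research question asks: "What is the effect of a coach supervised jump landing intervention program on jump landing technique of individual athletes". Under Jump landing technique, the protocol article says: "The researchers collect the jump-landing data at T0 and T1". The Measurements section confirms that these are the only two fixed occasions, three months apart.

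The Statistical analyses section gives the method: "The difference between the CG and IG regarding the JLS-system is calculated using Repeated Measures ANOVA (p < 0.05) for normally distributed data". The alternative is a Mann-Whitney "test (p < 0.05) for data which are not normally distributed". No baseline covariate is named, and no ANOVA term (group, time or group-by-time) is identified as the effect of the programme. The team level is stated for the injury analysis (multilevel Cox) and not for technique.

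Table 2 mixes item types. The knee, hip and ankle angles in the side view are recorded in degrees. The remaining items are scored 0/1 or 0/1/2. The section does not say which items count as normally distributed, but the angles are the natural candidates for the ANOVA.

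**The concern.** With two occasions, the group-by-time test compares mean change between the arms. That fixes the coefficient of T0 at 1, whatever the real correlation between T0 and T1. When the correlation is below 1, the coefficient is too large and part of the T0 noise is carried into the comparison. Using T0 as a covariate lets the data set the coefficient.

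The sentence also speaks only of a difference between the arms. Repeated Measures ANOVA produces more than one term that could be read that way, and they have very different power for an effect that appears only at T1.

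At stake is the precision of the technique result, which is the mechanism the programme targets. The power calculation covers injuries only, so nothing in the document shows that the technique comparison has precision to spare.

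**Working it through.** **Inputs from the protocol article.** Two occasions (Measurements); 24 teams, 240 athletes, intra-cluster correlation 0.20 (Sample size); equal randomisation (Recruitment). So there are 10 athletes per team, 12 teams and 120 athletes per arm.

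**Inputs not in the document, assumed.** The T0-T1 correlation rho, the technique effect in SD units, and the technique intra-cluster correlation (the injury value 0.20 is borrowed).

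**The plan's own figure.** It concerns injuries only: "A power calculation is carried out for the main outcome variable lower extremity injury incidence". For 78% against 39%, two-sided 5% and 90% power, the usual formula gives 32 per group (stated: 34). Then 34 × 2 × 1.2 = 81.6, or 82. The design effect is 1 + 9 × 0.20 = 2.8, and 82 × 2.8 = 229.6, so 23 teams of 10, or 24 as an even number. The figure holds up, but says nothing about technique.

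**Variance of the group contrast**, in units of the variance of one measurement, equal at T0 and T1:
- change (group-by-time): 2(1 − rho)
- T1 adjusted for T0: 1 − rho²
- ratio: (1 − rho²) / [2(1 − rho)] = (1 + rho)/2

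If the change test has 80% power, power after adjustment is Φ((1.960 + 0.842)/√((1+rho)/2) − 1.960). With the effect held at 0.6 SD and 120/2.8 = 42.9 effective athletes per arm, power is Φ(0.6 × √(42.9/(2V)) − 1.96), where V is the variance above.

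| rho | variance ratio | adjusted power when change has 80% | 0.6 SD: change v adjusted |
|---|---|---|---|
| 0.3 | 0.65 | 93.5% | 65% v 83% |
| 0.5 | 0.75 | 89.9% | 79% v 89% |
| 0.7 | 0.85 | 86.0% | 94.8% v 97.3% |
| 0.9 | 0.95 | 82.0% | about 100% for both |

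The third column implies a different effect size in each row; the last column holds it fixed. At rho 0.7 the gain is then 2.5 points.

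**Simulation with teams** (24 of 10, intra-cluster correlation 0.2, one athlete-level T0 slope, no team term in the fit). With team-level correlation equal to rho, the ratios were 0.65, 0.78, 0.87 and 0.96 at rho 0.3, 0.5, 0.7 and 0.9, close to the formula. With team means much more stable (team-level correlation 0.90 to 0.95, athlete-level 0.3 to 0.7), they were 1.04 to 1.10, so the gain was lost.

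**Why a team-mean covariate helps.** The arms differ between teams, so the correlation that matters is that of team means, R. Take athlete-level correlation 0.5 and team-level 0.95. The variance of a team mean is 0.2 + 0.8/10 = 0.28. The T0-T1 covariance is 0.2 × 0.95 + 0.08 × 0.5 = 0.23. So R = 0.23/0.28 = 0.82 and the ratio is (1 + 0.82)/2 = 0.91. Estimating one slope from 24 teams costs a factor of about 1 + 1/(24 − 4) = 1.05, giving about 0.96. The gain is small, but the reversal is gone. By the same sum, at R = 0.9 the ratio is 0.95 × 1.05 = 1.00, which is break-even.

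**The unnamed term.** The group term averages T0 and T1: variance (1 + rho)/2, with a T1-only effect halved. At 0.6 SD and rho 0.5, power is Φ(0.3 × √(42.9/1.5) − 1.96) = 36%.

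**The case against.** The strongest reply is that group-by-time is an accepted analysis of a question for which the trial was not powered, and that without rho the document cannot show a material loss. This largely stands. It limits the point to efficiency and makes it minor.

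A reader might infer more than the document supports:
- **That adjustment is never less precise.** This holds in large samples of independent athletes. It fails for a single athlete-level slope when team means are much more stable than athletes.
- **That the planned test has 79% power.** That figure includes a team correction that the Statistical analyses section does not state for technique. It shows the relative gain, not this trial's power.
- **That power is really 36%.** This needs the group term to be the one reported. The Jump landing technique section speaks of determining an improvement from the two occasions, which points to change. What stands is that the term is not named.
- **That the planned test is biased.** Nothing in the choice of change over adjustment shows that. Change and adjusted T1 estimate the same effect if the arms are comparable at T0. Allocation preceded contact with teams and athlete consent, so this comparability is an assumption, but it is a separate matter.

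It is also fair to say that a larger issue for technique is the unstated team level. With an intra-cluster correlation of 0.2 and equal correlations at both levels, an unclustered change test had a type I error of about 0.23 to 0.25 in simulation. Correcting that alone would still leave T0 unused and the effect unnamed.

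**Conclusion.** The point holds as a minor one. The stated method leaves T0 unused as a covariate and does not name the contrast that answers the second research question. The variance saving is 25% at rho 0.5, 15% at 0.7 and 5% at 0.9, provided that athletes are independent or that team-level and athlete-level correlations are similar. It shrinks to nothing, or to a loss of roughly 4% to 10%, with one athlete-level slope and very stable team means.

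The size rests on an assumed rho, and the power figures also on an assumed effect and a borrowed intra-cluster correlation. That the angles are the items concerned is inferred from Table 2. The injury analysis is not affected.

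**What to change.** In Statistical analyses, replace Repeated Measures ANOVA for the continuous joint angles by a linear mixed model of the T1 value on study group, with team as a random effect and with the athlete's own T0 value and the team-mean T0 value as covariates. State that the adjusted IG-CG difference at T1, with its 95% CI, is the technique effect.

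This is a change of wording and needs no new data, visits or athletes. It costs one or two extra parameters per outcome, including one team-level degree of freedom out of 24 teams. As shown above, that cost can use up the gain when team means are very highly correlated over time.

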### Recruitment

Of the 110 Flemish teams of the elite division, 24 teams are included and equally randomized to two study groups (Figure 1). Randomization and group allocation takes place before teams were contacted. This is done in order to avoid any spill over of the intervention while including teams. Through this method blinding of the teams to group allocation is secured.

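### The jump-landing technique (JLS) comparison is specified with athlete-level tests that ignore the randomisation of teams; the size of the resulting type I error inflation is not known from the plan.

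*Protocol article*

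**What the plan says.** The second research question asks: "What is the effect of a coach supervised jump landing intervention program on jump landing technique of individual athletes". Technique is filmed and scored for each athlete at baseline (T0) and at three months (T1).

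The Recruitment section states that "24 teams are included and equally randomized to two study groups". The Sample size section draws the consequence that "as teams serve as unit of randomization, a cluster effect should be taken into account", and reports that "an intra-cluster correlation coefficient of 20% was considered", "resulting in a total of 240 athletes from 24 teams is necessary at baseline".

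The Statistical analyses section applies this reasoning to injuries: "Because the unit of allocation was teams, we perform a multilevel Cox proportional hazard regression analysis". Its next paragraph turns to technique: "The difference between the CG and IG regarding the JLS-system is calculated using Repeated Measures ANOVA (p < 0.05) for normally distributed data", and otherwise a Mann-Whitney U "test (p < 0.05) for data which are not normally distributed". Team is not mentioned in that paragraph.

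**The concern.** Athletes in one team share a coach, training sessions and probably a filming session, so their scores, and possibly their changes in score, are likely to be correlated. A test that treats about 240 athletes as independent then understates the variance of the difference between groups, and its p-values are too small.

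A condensed article may leave details to a fuller document, but here the tests are named. One of them has no place for a team effect, and the paragraph just before gives the reason why one is needed.

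At stake is the second of the two research questions. A false positive would support the claim that coaches alone can improve landing technique, which is what the programme sets out to do.

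There is a smaller second problem. Repeated Measures ANOVA can test group by time, whereas Mann-Whitney U compares one value per athlete. The plan does not say whether that value is the T1 score or the T0-T1 change, so the outcome of a normality check may change the question being tested. Many JLS items are scored 0/1, and the genu varum/valgum items 0/1/2, so the non-normal branch will be used.

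**Working it through.** **Inputs from the protocol article.** 24 teams randomised equally, so 12 per group; 240 athletes, so 240/24 = 10 per team; dropout about 20%, so about 8 per team at T1; ICC 0.20, set for lower extremity injury incidence; JLS tested at p < 0.05 (two-sided assumed). No ICC is given for JLS.

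**The plan's own cluster adjustment.** Design effect DE = 1 + (m − 1) × ICC = 1 + 9 × 0.20 = 2.8. The plan's 34 per group is 68 athletes; 68 × 1.2 = 81.6, or 82. Then 82 × 2.8 = 229.6, which is 23 teams of 10, or 24 teams and 240 athletes once an even number is required. So 10 per team and a design effect of 2.8 match the plan's own reasoning for injuries.

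**Type I error when teams are ignored.** The naive standard error is too small by a factor √DE, so the actual two-sided error is 2 × [1 − Φ(1.96/√DE)]. For m = 10 and ICC 0.20: √2.8 = 1.673; 1.96/1.673 = 1.171; 2 × [1 − Φ(1.171)] = 24.1%.

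| Assumed ICC of the value tested | DE, 10 per team | Error, 10 per team | DE, 8 per team | Error, 8 per team |
|---|---|---|---|---|
| 0.02 | 1.18 | 7.1% | 1.14 | 6.6% |
| 0.05 | 1.45 | 10.4% | 1.35 | 9.2% |
| 0.10 | 1.90 | 15.5% | 1.70 | 13.3% |
| 0.20 | 2.80 | 24.1% | 2.40 | 20.6% |

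**Simulation check** (12 v 12 teams, no group difference; 20,000 runs, of which 3,000 for Mann-Whitney). With 10 per team and ICC 0.20, an athlete-level t-test rejected in 24.4% and Mann-Whitney in 23.8%; a t-test on team means rejected in 5.1%. With 8 per team the athlete-level tests gave 21.3% and 21.8%.

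**Which ICC matters.** In a two-group, two-time Repeated Measures ANOVA the group-by-time test is equivalent to a t-test on change, so it depends on the ICC of the T0-T1 change, not of the score. Simulation with score ICC 0.20, 10 per team and an assumed within-athlete correlation over time of 0.6 gave:

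| Correlation of team effects, T0 to T1 | Implied ICC of change | Group-by-time error | Group main-effect error |
|---|---|---|---|
| 1.0 | 0 | 5.0% | 26.9% |
| 0.9 | 0.06 | 11.2% | 26.4% |
| 0.8 | 0.11 | 16.8% | 25.7% |
| 0.6 | 0.20 | 24.2% | 24.8% |

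Fully stable team effects thus protect the group-by-time test but not the group main effect. By the same reasoning they would not protect a Mann-Whitney test on T1 scores alone.

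**The case against.** The strongest objection is to the number. A reader might infer that the technique test has an error rate of 24%, because the protocol assumes an ICC of 0.20. The documents do not support that. The 0.20 was set for injury incidence, nothing is said about clustering of JLS, and the planned dropout lowers the figure to about 21% even if 0.20 applied. For group by time, a score ICC of 0.20 is compatible with almost no inflation if team differences persist unchanged. All of this stands: 24% illustrates one assumption and is not a property of the plan.

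It can also be said that if the programme changes nothing in any team, coaching it cannot create correlated change. That is right as far as it goes. Clustering under the null would then have to come from usual training, filming sessions, or programme effects that differ between teams and average to zero. The plan's weekly record of which exercises intervention coaches actually used allows for differences in delivery, so stability of team effects cannot be taken for granted.

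Two further inferences go too far. One is that reported confidence intervals for technique are too narrow: the protocol promises 95% intervals for hazard ratios only and p-values for JLS. The other is that Mann-Whitney discards the baseline: change scores could be entered, and the text does not say.

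Finally, the stated objective and the sample size concern injuries, whose analysis is already multilevel. That lowers the priority of the point but does not answer it.

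**Conclusion.** The analysis stated for JLS is wrong for a cluster-randomised design and inconsistent with the protocol's own reasoning for injuries. The inflation is unknown. On assumed ICCs of 0.02 to 0.20 for the value tested, the actual error of a nominal 5% test runs from about 7% to 24% with 10 athletes per team, and is about 21% at the upper value with 8 per team. These figures assume equal team sizes and two-sided tests. A group-by-time test stays close to 5% only if team differences are fully stable from T0 to T1. The value entering the Mann-Whitney test is an unresolved ambiguity, not a demonstrated error. Because the injury outcome, on which the trial is sized, is unaffected, this should be fixed but does not threaten the main conclusion.

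**What to change.** Replace the JLS sentence with an analysis by team for each outcome:

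- **Continuous measures (joint angles, any summed score):** a linear mixed model of T1 on group, T0 and sex, with a random intercept for team and small-sample degrees of freedom (24 − 2 = 22, or fewer once sex is fitted as a team-level covariate).
- **0/1 items:** a logistic mixed model, or GEE clustered on team with a small-sample correction, which 24 teams require.
- **0/1/2 items (genu varum/valgum):** dichotomise by a rule fixed in advance and analyse as above, or treat as categorical in a multinomial mixed model.
- **Where normality fails:** a team-level permutation test on the T0-T1 change, permuting whole teams within sex, so that the question stays the same whichever branch is used.

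The cost is analysis wording and somewhat more effort in fitting. No extra data are needed. The price is generally larger p-values and less apparent precision for the technique outcome.

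### The technique question has no fixed endpoint: the JLS-system has 20 to 30 items, each test is at p < 0.05, and no multiplicity control or team level is stated

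*Protocol article*

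**What the plan says.** The Research questions section of the Protocol article asks two things. The second is: "What is the effect of a coach supervised jump landing intervention program on jump landing technique of individual athletes".

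Under Jump landing technique, "all jumps are evaluated through a predefined list of criteria, the JLS-System (Jump-landing Scorings system) (Table 2"). Each athlete makes three jumps at T0 and three at T1. Table 2 then lists the criteria:

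- **Front view:** 10 items. Eight are scored 0/1, for example "Loss of balance not present or doubt: 0 Loss of balance present: 1". Two, knee alignment at take-off and at landing, have three codes: 0 for aligned, then "Patella lateral from the perpendicular: (1 = varum) Patella medial from the perpendicular: (2 = valgum").
- **Side view, marked as right and left:** 10 items. Six are knee, hip and ankle angles, each read at two instants ("Knee angle at first foot contact Knee angle at maximal knee flexion") and recorded in degrees with no score attached. Four are scored 0/1.

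The article gives no total, no key item and no rule for combining the three jumps.

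The Statistical analyses section states: "The difference between the CG and IG regarding the JLS-system is calculated using Repeated Measures ANOVA (p < 0.05) for normally distributed data", and otherwise by a Mann-Whitney "test (p < 0.05) for data which are not normally distributed". The multilevel model with teams as clusters is described for the Cox analysis of injuries. No team level is named for the technique comparison.

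**The concern.** The analysis section fixes the tests and the significance level but not the variable to which they apply. A list that mixes binary scores, three-category codes and degrees is not one variable. Choosing the test by distribution also points to more than one, because a 0/1 item cannot be normally distributed while an angle may be.

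If several or all items are each tested at 5%, a programme with no effect on technique could well produce a significant item, and nothing in the plan says whether that would answer the question. An improvement in technique is the mechanism by which the programme is meant to prevent injury. A chance finding would therefore be easy to read as support for the programme.

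Teams were randomised. An athlete-level test that ignores teams runs above its nominal 5% whenever team-mates resemble each other on the outcome.

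**Working it through.** The plan states no family-wise error rate for technique, so there is no figure of its own to reproduce.

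**Inputs from the article**
- Items (Table 2): 10 front view + 10 side view = 20. With sides kept apart: 10 + 2 × 10 = 30. By scale, the 20 are 12 binary, 2 three-code and 6 angles.
- Level (Statistical analyses): 0.05 per test.
- Team size (Sample size): 240 athletes / 24 teams = 10.

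**Assumptions, not in the article**
- Each item is tested separately, with no true effect on any item.
- The correlation between test statistics is unknown, so a range is shown.
- The ICC of the technique measures is unknown.

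**Step 1: independent items.** The chance of at least one p < 0.05 is 1 − 0.95^k.
- k = 20: 1 − 0.95^20 = 0.642, with 20 × 0.05 = 1.0 false positive expected.
- k = 30: 1 − 0.95^30 = 0.785, with 30 × 0.05 = 1.5 expected.

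**Step 2: correlated items.** Simulation of equally correlated normal test statistics, 200,000 draws, two-sided 5%:

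| Correlation | 20 items | 30 items |
|---|---|---|
| 0 | 64% | 79% |
| 0.3 | 54% | 66% |
| 0.4 | 48% | 59% |
| 0.5 | 42% | 51% |
| 0.7 | 29% | 34% |

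If only left-right pairs are strongly correlated (0.9), 30 items give 71% with the others independent and 61% with the others at 0.3.

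**Step 3: fewer tests.** If the scored items were summed and only that sum and the six angles were tested (k = 7), independent tests would give 1 − 0.95^7 = 0.302.

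**Step 4: ignoring teams.** The design effect is DE = 1 + (10 − 1) × ICC. The actual error of a nominal 5% test is 2 × [1 − Φ(1.96/√DE)]. The ICC is that of whatever is compared between arms (T1 value or change).
- ICC 0.05: DE = 1.45, error about 10%.
- ICC 0.20 (the article's injury value, borrowed for illustration): DE = 2.8, error about 24%.

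With ICC 0.05, the chance of at least one false positive is 89% (20 items) or 96% (30 items) if independent, and 49% or 56% at correlation 0.7.

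**Step 5: after the change.** One pre-specified endpoint, analysed with team as cluster, has a nominal 5% error. With independent tests that each hold their level, 0.05/20 = 0.0025 or 0.05/30 = 0.0017 per item gives a family-wise error of about 4.9%. This is the Bonferroni level, at which Holm starts.

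**The case against.** The strongest reply is that this is a condensed article and that a full protocol or analysis plan may define a total score, a key item or an adjustment. That is a fair limit on the point: the missing total alone would not be a finding. What stands is that the article prints the whole instrument and fixes the tests and the level, and these together do not yield one answer.

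A second reply concerns the number of tests. A reader might infer that the plan prescribes one test per item. It does not: it refers to the JLS-system in the singular and never mentions items. The scored criteria all run in one direction, with 0 for correct or doubtful, so an error sum is conceivable. Whether the varum and valgum codes are weights or labels is not stated. But the six angles have no score and cannot enter such a sum as printed, and the choice of test by distribution implies more than one variable. Several tests remain the natural reading, though not necessarily 20 to 30.

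A third reply is that the items are likely to be correlated: joint angles at the same instants, and two sides of the same landing. This is why a range is given. It lowers the risk but does not bring it near 5%.

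**Conclusion.** The point holds in conditional form. As stated, the plan gives technique 20 to 30 candidate items, tests at p < 0.05 each, no multiplicity control and no team level. If the items are tested separately and none is truly affected, the chance of at least one false positive is about 64% to 79% under independence and 29% to 34% at correlation 0.7. Even the lowest of these is nearly six times the nominal 5%. It is higher again if technique clusters by team.

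A reader might go further and say that a chance finding is more likely than not. The documents do not support that without conditions. Leaving clustering aside, it holds only up to a correlation of roughly 0.35 with 20 items or 0.5 with 30, and the article gives no correlations.

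The main outcome, lower extremity injury incidence, has its own team-level Cox analysis and is not touched by this point.

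**What to change.** In the Statistical analyses section:

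1. Pre-specify one technique endpoint, with its rule for the three jumps and the two sides, or apply Holm across all items that may be claimed. The endpoint could be a defined error score, a key angle or the valgus item. The choice belongs to the investigators. A sum of the binary items alone would leave out the joint angles, which bear most directly on the stiff landing that the Background names as a risk factor.
2. Compare the T1 value between arms with the T0 value as covariate and team as cluster.
3. Report the remaining items and angles descriptively, with confidence intervals.

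This takes a few sentences and uses only data already planned. The cost is small: unadjusted p-values for single items can no longer be claimed as findings.
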